### Counsellors

All counsellors in the trial are accredited either by the British Association for Counselling and Psychotherapy (BACP) or the UK Council for Psychotherapy (UKCP) and are employed by the UCS. A minimum of 6 counsellors (2 control, 4 intervention) will be assigned to support the trial, both in development and delivery, and will deliver either the enhanced intervention or TAU condition based on their preference. Counsellors will also be trained by a researcher in the details specific to the intervention they are allocated to (see “Training” section below). When entering the trial, counsellors will provide a statement describing their model of practice and specific therapeutic style. The aim of collecting these statements is to improve the reporting quality when describing the therapy available, and to aid development of a clinical manual as an outcome of the feasibility trial.

Counsellors will also be provided with the BACP competency framework [14] for the University and College Counselling (UCC) context together with the most recent service clinical handbook in order to ensure best practice. Whilst these handbooks will be used to reinforce clinical competency throughout the trial, one outcome of the feasibility trial is to refine the clinical frameworks and develop a manualised training programme for delivering the enhanced intervention in a university counselling setting. For the present study, clinical practice will be reinforced throughout the trial with fortnightly team meetings with the head of service, onsite researcher and counselling team. There will also be optional daily drop-in sessions for members of the counselling team to query issues with the onsite researcher.

### Measures

The timeframe for administering measures has been summarised in Table 1 and in a Standard Protocol Items: Recommendations for Interventional Trials (SPIRIT) diagram in Fig. 2. The clinical outcome measures and primary and secondary feasibility measures have been detailed below.

**Table 1 Tab1:** Summary and timeframe of measure administration

Measure	Clinical assessment	Consent session	S1	S2	S3	S4	S5	S6	Last session^a^	3-month follow-up	6-month follow-up
CORE-10	×		×	×	×	×	×	×	×		
CCAPS-62	×										
CCAPS-34			×	×	×	×	×	×	×		
PHQ-9		×								×	×
GAD-7		×								×	×
CD-RISC 10		×								×	×
WAI-12					×						
CSQ-8									×		

^a^This may be any session number beyond session 2 as the number of sessions will vary across clients and will be dependent on client-counsellor agreement

**Fig. 2 Fig2:**
[figure not shown]
SPIRIT diagram displaying schedule of enrolment, interventions and assessments of the CASELOAD feasibility trial

#### Clinical outcomes

##### Clinical Outcomes in Routine Evaluation (CORE-10)

The 10-item Clinical Outcomes in Routine Evaluation outcome measure [15] will be administered at the initial clinical assessment (pre-intervention) and at every counselling session, to measure changes in general psychological functioning. Items refer to the previous week and are scored on a 5-point Likert scale (0 = “not at all”; 4 = “most or all of the time”), whereby higher scores indicate higher symptom severity. CORE-10 is a shortened version of the Clinical Outcomes in Routine Evaluation - Outcome Measure [16] which has been used extensively in mental health services in the UK for over a decade. The 10-item version has been validated against CORE-OM, has been shown to be sensitive to change and can be used to determine whether a client meets membership of a clinical population (score ≥11).

##### Counseling Center Assessment of Psychological Symptoms (CCAPS)

CCAPS [17] is a measure developed in the USA specifically for the student college population and will be administered with CORE-10 at the initial clinical assessment (pre-intervention) and every counselling session to measure changes in student-specific mental health concerns. Items refer to the previous 2-week period and are scored on a 5-point Likert scale (0 = “not at all like me”; 4 = “extremely like me”), whereby higher scores indicate higher symptom severity. In addition, because CCAPS was designed for UCSs to measure student mental health, it also monitors changes in the following areas: depression, generalised anxiety, social anxiety, academic distress, eating concerns, hostility, substance abuse, family distress and suicide ideation. Within each construct, CCAPS determines clinical membership (e.g. clinical versus non-clinical) and severity (e.g. low versus elevated clinical severity), which are detailed in the CCAPS clinical guide. Finally, CCAPS has been validated in UK samples through use in UK UCS and in a recent doctoral research project [18].

##### Patient Health Questionnaire (PHQ-9) and Generalised Anxiety Disorder scale (GAD-7)

The 9-item Patient Health Questionnaire [19] and 7-item Generalised Anxiety Disorder scale [20] will be administered in the research interview, after treatment completion (3-month follow-up), and at follow-up (6-month follow-up), to measure depression and anxiety to determine eligibility. Clients who reach moderate clinical criteria for depression (score ≥10) or anxiety (score ≥10) will be invited into the trial. These measures will also be administered at 3 and 6 months after the consent date to monitor changes in symptoms. Items on PHQ-9 and GAD-7 refer to the last 2 weeks and are scored on a 4-point Likert scale (0 = “not at all”; 3 = “nearly every day”) whereby higher scores indicate higher severity. Both measures have been used widely by mental health services to measure depression and is mandatory in the Improving Access to Psychological Therapies (IAPT) initiative in the National Health Service (NHS). The purpose of using these measures in the current study is to benchmark outcomes against primary care services accessed by the general clinical population in order to allow comparisons between student and non-student clinical populations.

##### Connor-Davidson Resilience Scale (CD-RISC 10)

The 10-item Connor-Davidson Resilience Scale [21] will be administered in the research interview (pre-treatment), after completion of counselling (3-month follow-up), and at follow-up (6-month follow-up) to measure changes in resilience. Items refer to the previous month and are scored on a 5-point Likert scale (0 = “not true at all”; 4 = “true nearly all of the time”), whereby higher scores demonstrate higher resilience. By measuring resilience, the CD-RISC 10 also measures an individual’s ability to tolerate change, pressure, personal problems, negative outcomes, painful feelings and illness. The CD-RISC 10 is a short version of the original CD-RISC 25, has good internal consistency (Cronbach alpha .85), has good construct validity (e.g. resilience moderates impact of maltreatment on mental health) and has been demonstrated to have a factor structure which is more stable than CD-RISC 25 [21, 22].

###  Selection of a well-being app

There are a large variety of smartphone apps that offer tools and support for improving wellbeing via a range of common features. Whilst there are many apps to choose from they are typically based on Cognitive Behavioural Therapy (CBT) and mindfulness to offer tools for (1) tracking daily moods and behaviours, (2) reflecting on diary entries, (3) setting goals, (4) completing exercises to relax and defuse negative emotions and (5) interacting with anonymous online support communities for peer-led support. Some of the most promising well-being apps include Pacifica (http://www.thinkpacifica.com/), Headspace (https://www.headspace.com/) and Buddy App^3^. To aid the decision of selecting a well-being app for the current study, the following criteria were applied: (1) applicable to university students (e.g. providing tools to help manage social anxiety, depression, stress and general aspects of student lifestyle); (2) demonstrates potential to be integrated with face-to-face counselling; (3) available across iOS and Android platforms; (4) offers a range of features overlapping with other well-being apps; and (5) provides a promising free version to permit continued service use after the trial without financial implications.

Based on these criteria, the Pacifica app was selected and evaluated with a volunteer student sample (see next section), before it was implemented in the current feasibility trial. Whilst the app offers a free version with restricted variations of each feature (e.g. only 3 relaxation exercises compared to 8–10), the full version was used in both the evaluation study and current study to allow robust evaluation of all available features representative of other well-being apps. Furthermore, a secondary feasibility outcome will explore the added gain of using the full version compared to the free version. In both studies, a series of annual app subscriptions were purchased and provided to participants as unique gift codes. All payments were subject to the standard fee for public users and no financial incentives or waivers were provided by the Pacifica development team. Whilst the present study utilised a specific app (i.e. Pacifica), our reasoning was that this app was used in the trial as representative of well-designed apps in the field rather than being an evaluation of Pacifica per se.

### Evaluation of well-being app (Pacifica)

To aid the training, risk monitoring and intervention delivery of a well-being app in the current study, a preliminary evaluation study was conducted with the well-being app (ethical approval reference: University of Sheffield, Department of Psychology, 006727). The aims of the evaluation study were twofold: (i) to explore students’ experiences of using the well-being app to determine features that require additional support and (ii) to explore counsellors’ experiences of using the well-being app to understand how various features could compliment counselling. The student sample comprised 20 healthy volunteers (UG and PG) whereas the counsellor sample included members of the counselling team who were already scheduled to engage with the feasibility trial. Students attended a research session to learn about each app feature and were encouraged to use the app daily for 7 days. Students were instructed to use all app features once before selecting 2–3 features to use throughout the week. At the end of the week, students completed an evaluation form, inputted their app data into a spreadsheet and described their overall experience to a researcher in an interview. Based on their feedback and availability, 8 students (UG and PG with positive and negative experiences) attended a focus group to discuss their experiences and suggestions for improving the app.

The counsellor sample comprised 6 counsellors from the UCS who were scheduled to deliver the enhanced intervention condition of the feasibility trial. After attending a one-to-one research session to learn about each app feature, counsellors were instructed to use the app daily for 7 days. During this time, counsellors were advised to use all app features and to consider (1) clients who may benefit from using each feature and (2) how the app could be integrated between and within counselling sessions. At the end of the week, counsellors attended a focus group to discuss the feasibility of clients using the app alongside counselling and whether it would be feasible to review app activity during counselling sessions. Feedback from student and counsellor groups shaped the enhanced intervention and refined staff training for the current feasibility trial.

### Training

Prior to commencement of the trial, all participating counsellors will attend a one-to-one training session with a researcher to address the following: (1) knowledge of the trial research process; (2) language use for describing the trial to students; (3) counsellor expectations; and (4) areas of concern. Training sessions with counsellors in the enhanced intervention condition will additionally cover (1) willingness to audio record therapy sessions, (2) client consent to audio record therapy sessions, (3) therapeutic rationale for various app features and (4) research rationale for supplementing counselling with guided use of a well-being app. Following this, counsellors will be invited to a condition-specific training session to reduce discussion between counsellors and ensure that the enhanced intervention is delivered by counsellors who are engaged and committed to using a well-being app alongside therapy. Therefore, training with counsellors in the TAU group will only address research requirements (e.g. recruitment) and will focus on the research rationale for using an active control group and language use for recruitment.

To encourage integration of the app during counselling sessions and encourage discussion of client app activity, counsellors in the enhanced intervention will be provided with computer tablets to use during therapy sessions to review and discuss app features with clients. During training, counsellors will practice using the tablet to navigate through various app features and a range of role play exercises will be used to mimic different therapy scenarios. The tablet will also be used to audio record therapy sessions and counsellors will practice using the recording feature during training. The training session will be guided with a manual which will provide examples of how to address various scenarios as well as brief scripts to prompt counsellors during training. Script examples include the following: inviting students to book a research interview; describing the intervention in the first counselling session; confirming participant’s involvement in the study at the first counselling session; confirming permission to audio record; commencing app discussion during therapy sessions; reviewing app activity; inviting participants to use the computer tablet; and supporting participants who decide to withdraw from the trial. Counsellors will also be encouraged to make notes in their training manual to cater the examples to suit their therapeutic style.

These practical sessions aim to ensure that counsellors are confident with the technology requirements and feel at ease using the app in a therapeutic context. Therefore, counsellors will be put into pairs to practice each example and will alternate between client and counsellor roles. More specifically, when counsellors are in the role of a hypothetical client they will be asked to mimic potentially challenging behaviours they have previously experienced during sessions with their own clients. These exercises aim to challenge counsellors before they start using the app with clients. Counsellors will also have the opportunity to role-play examples with the onsite researcher throughout the trial to build confidence and refresh training. At the end of the training session, counsellors will complete a feedback form detailing their confidence in executing technical, administrative and therapeutic requirements of the trial. This information, combined with feedback from the focus group at the end of the trial, will be used to improve the manualised training for the definitive trial.

#### Technology acceptability

Despite the prevalence of technology being integrated into physical and mental health interventions, staff acceptability has been an ongoing issue and can hinder implementation [23, 24]. The current study aimed to reduce threats to staff acceptability by delivering a training programme to address various aspects of acceptability. For example, according to the technology acceptability model, there are several factors which influence technology acceptability in healthcare professionals including performance expectancy, effort expectancy, computer anxiety, computer self-efficacy and computer attitude [25]. For instance, according to Schaper and Pervan [25], performance and effort expectancy refer to the perceived ability of the technology to assist with an individual’s ability to fulfil their duty and the ease at which it can be achieved. In preparation for training in the current study, therapists used various app features daily for 1 week and were asked to consider how certain features would complement their therapeutic style. Therapists also shared their ideas in group training to inform other therapists with similar therapeutic models. Regarding effort of use, therapists were required to review a client’s app usage for a few minutes every session as a minimum but ultimately had the flexibility and responsibility to use the app as they deemed appropriate. Regarding computer anxiety and self-efficacy, in addition to the group training, therapists received ongoing one-to-one sessions with the primary researcher whom had a daily presence at the counselling service throughout the trial. Finally, regarding attitude and therapist engagement, the intervention therapists were selected based on (1) initial recommendations from the head of service and (2) expressed interest from therapists.

### Therapist effects

There has been conflicting evidence exploring the impact of therapist effects on trial outcomes and there are various methods for estimating therapist effects [26]. Nonetheless, exploring therapist effects is important in implementation studies and for considering differences in treatment delivery across therapists. Due to the underpowered sample of the current feasibility trial, therapist effects for each of the quantitative outcomes will be estimated with intra-therapist correlations.

### Counselling interventions

All participants will receive an active treatment in line with standard practice and will not be disadvantaged by participating in the trial. Participants will have access to the standard level of care at Sheffield UCS, which includes a wait period of typically 3–5 working days for the initial clinical assessment and 8–10 days between ongoing therapy sessions. This wait period varies throughout the year but the service agreement offers first contact within 10 days, and this is typically shorter than the NHS waiting times.

### Counselling (TAU)

Up to 6 sessions of face-to-face counselling will be offered to participants in line with standard practice at Sheffield UCS. Sessions will be 50 min in length and the frequency of sessions will be determined through client-counsellor discussions. If participants require more than 6 sessions, treatment will continue outside of the trial and will be supported by the counselling centre. On such occasions, trial data will only be collected up to session 6.

### Counselling supplemented with well-being app (enhanced intervention)

Up to 6 sessions of face-to-face counselling will be offered to participants in line with standard practice at the UCS. Sessions will be 50 min in length and the frequency of sessions will be determined through counsellor-client discussions. As well as the standard level of care, counselling sessions will be supplemented with discussion and guided use of a well-being app to promote engagement within and between face-to-face sessions. Clients and counsellors will have the opportunity to use the app on a computer tablet during counselling sessions to facilitate discussion and to aid the decision process for setting goals and reviewing client progress. Through these discussions, counsellors will review client app activity and guide them through various app features to decide which activities would be beneficial to use between face-to-face sessions. App features may include (1) daily behaviour tracking for mood, sleep, exercise, relationships, hygiene, water/caffeine/alcohol consumption, medication use and time spent outside; (2) reflective thinking through guided CBT, thought journaling, mindfulness and positive visualisation; (3) guided relaxation with breathing, meditation and body scan exercises; (4) peer-led support through anonymous online communities and private groups; and (5) setting/tracking short-term and long-term goals.

The app will provide daily prompts to encourage participants to log their mood/behaviour, but completion of various exercises relies on participants deciding when to use a feature, for example at the suggestion of their counsellor. Counsellors will also encourage participants to prepare for each face-to-face counselling session by reflecting on their diary entries and deciding on what they would like to address in the session. This reflective exercise may also occur at the start of each therapy session for participants who prefer to reflect on their activities with the support of their counsellor. During face-to-face sessions, counsellors will be encouraged to review app activity by asking participants to access their app account on the computer tablet, discuss participant’s reflections and progressively adjust goals or exercises where appropriate.

#### Audio recording of sessions

Counselling sessions in the enhanced intervention will be audio-recorded, with participant consent, using the tablet in order to be more discrete than traditional recording equipment. Written consent for recording sessions will initially be sought during the research interview when participants join the trial. However, verbal consent will also be sought by counsellors at the start of each session to allow participants to opt-out of recording a particularly distressing counselling session. Sessions in the TAU condition will not be audio recorded to align with standard practice and because analysis is specific to discussing app activity, which is dependent on the enhanced intervention.

### Primary feasibility measures

The yield of the feasibility trial is a series of specific primary and secondary outputs relating to a range of components that will inform the definitive trial. The primary outputs are recruitment, treatment preference, randomisation acceptability, treatment satisfaction and completion rate of follow-up measures. The secondary outputs are: app usage, intervention fidelity, client characteristics, therapeutic alliance and academic coping. Each of these primary and secondary outputs is described next.

#### Recruitment

The recruitment period for a definitive trial will be estimated from the current study by exploring the required time needed to reach 40 participants, whilst also considering the participant drop-out rate and counsellor availability. Seasonal service demands will also be explored to distinguish peak service demand and to advise on the optimal time of year to implement a definitive trial. Service demand will be assessed by comparison of the annual reports provided from the service.

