### Allocation

This study is a non-randomised feasibility trial that aims to address the acceptability of randomisation prior to planning a pilot trial in preparation for a future definitive trial. Therefore, allocation will be based on counsellors’ clinical judgement of each student’s unique situation and primary reason for approaching the service. This will inform the acceptability and feasibility of randomising for the pilot trial. Participant allocation will also depend on whether the assessing counsellor is involved in the trial (based on availability) and whether the counsellor is participating in the provision of the enhanced intervention or TAU condition. Because the enhanced intervention relies on counsellors that are committed and trained to supplement counselling with a well-being app, participants assessed by counsellors in the TAU condition will not have the opportunity to join the enhanced intervention. However, participants assessed by counsellors in the enhanced intervention may be allocated to either condition as determined by their counsellor. Similarly, participants assessed by counsellors providing the enhanced intervention for whom the app is deemed inappropriate (e.g. client presents with inappropriate/excessive technology use or risk negative exposure to online communities for self-harm) will be allocated to TAU.

Considering these design elements, allocation will depend on the following factors: (i) whether the initial clinical assessment is with a counsellor who is part of the trial; (ii) whether the assessing counsellor is allocated to provide the enhanced intervention or TAU condition; (iii) the clinical judgement of the counsellor regarding whether participating in the trial would be appropriate for the client; and (iv) the clinical judgement of the counsellor regarding which intervention would be appropriate for the client. Whilst this allocation procedure is reliant on a counsellor’s clinical judgement, it is arguably the most appropriate allocation method for a non-randomised study and it keeps the client’s welfare in the forefront. Integrating a well-being app with face-to-face counselling with students experiencing moderate anxiety or depression is a new development with limited understanding of the implications. Therefore, using clinical judgement to inform the allocation will better monitor risk and feasibility metrics which counsellors will document to inform the screening criteria of a future randomised trial.

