#### Randomisation acceptability

Once participants state their treatment preference and are informed of their actual treatment allocation, they will be asked whether being randomised to that condition increases the probability of them withdrawing from the study. This information, combined with the recruitment metrics, will be used to estimate the recruitment period and inform whether randomisation in a definitive trial would negatively impact on uptake.

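### The recruitment estimate for the definitive trial counts clients for whom the counsellor has ruled out the app, so it overstates the randomisable rate if any are enrolled; the seasonal source is also not fixed

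*Protocol article*

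**What the plan says.** Recruitment is listed first among the primary outputs (Protocol article, Primary feasibility measures). Its Recruitment subsection states: "The recruitment period for a definitive trial will be estimated from the current study by exploring the required time needed to reach 40 participants", with two qualifications, "whilst also considering the participant drop-out rate and counsellor availability". The Randomisation acceptability subsection adds clients' own answers on whether their allocation makes withdrawal more likely: "This information, combined with the recruitment metrics, will be used to estimate the recruitment period". The Allocation section also feeds treatment preference and existing app use, noted at the research interview, into the recruitment rate.

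The Allocation section sets out who enters which arm. Under it, "participants assessed by counsellors providing the enhanced intervention for whom the app is deemed inappropriate" are placed in TAU. They are not screened out. Separately, "participants assessed by counsellors in the TAU condition will not have the opportunity to join the enhanced intervention".

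The Recruitment subsection also aims to find the peak of demand and to advise on the best time of year for the definitive trial. The source it names is: "Service demand will be assessed by comparison of the annual reports provided from the service".

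**The concern.** The time to reach 40 is to be carried forward to a randomised trial, but the 40 are defined by entry to a non-randomised study. A client whose counsellor has ruled out the app can enter this study and could not properly be randomised. Each such client shortens the observed time to 40 without adding to the pool that the definitive trial can draw on. If nobody separates them, the next trial is planned on a rate that is too favourable.

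The seasonal aim raises a second, smaller question. A peak within the year can be found only from figures broken down within the year, and the article does not say that the named source has them. Service demand is also not the same quantity as recruitment of eligible, consenting clients.

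**Working it through.** **No figure to reproduce.** The target of 40 is given without a power or precision basis, and no recruitment rate is stated. The check is therefore on what the 40 contains.

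**Do app-unsuitable clients count toward the 40?**
- The exclusions under Study population are high risk, current therapeutic support, and complex problems beyond anxiety or depression. App-unsuitability is not among them.
- The Allocation section separates two counsellor judgements: whether the trial suits the client, and which condition suits the client. A client can pass the first and be ruled out of the app by the second.
- Such a client goes to TAU within the trial and so counts.

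**Does a stated adjustment remove them?**

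| Adjustment | Section | Captures a counsellor's ruling-out of one arm? |
|---|---|---|
| Drop-out rate | Recruitment (primary measures) | No |
| Counsellor availability | Recruitment (primary measures) | No |
| Client's stated likelihood of withdrawing | Randomisation acceptability | No, it is the client's view |
| Client preference and existing app use | Allocation | No |

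**Size.** Let T be the time to 40 and f the share of the 40 unsuitable for one arm. The raw rate is 40/T and the randomisable rate is 40(1-f)/T. The overstatement is their ratio, 1/(1-f), and the time to 40 randomisable clients lengthens by the same factor. The values of f are assumed.

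| f | Randomisable, 40(1-f) | Overstatement, 1/(1-f) |
|---|---|---|
| 0% | 40 | x1.00 |
| 5% | 38 | x1.05 |
| 10% | 36 | x1.11 |
| 20% | 32 | x1.25 |
| 30% | 28 | x1.43 |
| 50% | 20 | x2.00 |

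For illustration, a recruitment period planned at 12 months would need 12 x 1.25 = 15 months at f = 20%.

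**Clients with no assured judgement.** The Counsellors section gives a minimum of 2 TAU and 4 enhanced counsellors. With equal caseloads (assumed), clients of TAU counsellors number 40 x 2/6 = 13.3. The app evaluation section mentions 6 counsellors scheduled for the enhanced arm; with 2 TAU counsellors the figure would be 40 x 2/8 = 10. So for about 10 to 13 of the 40, suitability for both arms would not be established.

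On the 2:4 split, suppose 20% of the 26.7 clients of enhanced-arm counsellors are app-unsuitable. If every client of a TAU counsellor is randomisable, 13.3 + 26.7 x 0.8 = 34.7 remain (x1.15). If the same 20% applies to them, 32 remain (x1.25).

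**Scale against sampling error.** If arrivals follow a constant-rate Poisson process, 2 x rate x T has a chi-square distribution with 80 degrees of freedom. The 95% limits for a rate from 40 arrivals are then 0.71 and 1.33 times the estimate. Since 1/(1-f) = 1.33 at f = 25%, the bias passes the upper limit only above about 25%.

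**The case against.** The strongest reply is that the data for a correction are largely planned. The Allocation section has counsellors document metrics for the screening criteria of a later randomised trial. Client characteristics builds an appropriateness checklist expected to shape the definitive trial's inclusion criteria. This stands as far as it goes, but neither section links that information to the recruitment estimate. TAU allocation is no substitute for a recorded judgement, because enhanced-arm counsellors may place a client in either condition.

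Second, f may be small. Counsellors can keep a client out of the trial altogether, and the exclusions for risk and complexity may remove some app-unsuitable clients beforehand. Using only some of the service's counsellors also slows accrual. This stands too: a net bias in the overall recruitment time is not shown, only the upward effect of this one component.

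Third, a randomised pilot is to come before the definitive trial and could observe randomised accrual directly, and much of the plausible bias lies within the sampling error of 40 arrivals. Both are true and lower the stakes. Even so, the bias runs one way and adds to the sampling error, and recording one item avoids it.

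A reader might infer that clients of TAU counsellors could never be randomised, which on the 2:4 split would leave 26.7 of 40 and an overstatement of x1.50. The documents do not support this. Those clients are confined to TAU by who assessed them, and could be randomised under another counsellor arrangement.

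A reader might also infer that annual reports cannot inform the timing of recruitment. That is not shown either: such reports may contain monthly or termly counts, and the article does not say whether they do.

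**Conclusion.** The point holds conditionally. As written, the estimate counts clients for whom a counsellor has ruled out one arm, and no named adjustment takes them out. The randomisable rate is overstated by 1/(1-f) whenever f is above zero and the estimate is left uncorrected: x1.11 to x1.43 over an assumed 10% to 30%. It would be going too far to say that the estimate will certainly overstate, since f is not given and could be near zero. Clients of TAU counsellors are of unknown randomisability.

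On season, the fault is that the within-year resolution of the source is not stated. Yearly totals alone could not answer the question; reports with monthly or termly counts could describe demand, though not trial recruitment. This is a worthwhile, low-cost improvement to a primary output and does not undermine the study.

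**What to change.** 1. Have trial counsellors record, for each client they assess, one of three categories with a reason: *either condition*, *TAU only* or *app only*. Use the same short criteria in both counsellor groups. This is a record only and leaves allocation and care as they are.
2. In the Recruitment subsection, commit to reporting the recruitment rate, with a confidence interval, for clients suitable for either condition, beside the raw time to 40. Show clients with no suitability judgement as a separate group.
3. For season, name monthly referral counts from the service's electronic clinical scheduling system (mentioned under Managing risk and adverse events) as the source, and report trial recruitment per referral by calendar month.

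The cost is one checklist item, brief guidance so that both counsellor groups apply the criteria alike, and one data extract. The stated rate becomes less favourable if unsuitable clients are found.
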